### Selection of participants

#### Recruitment

Potential participants will be screened by the surgical and anaesthetic teams who will then inform a member of the research team of the potential availability of the patient for the trial. A member of the research team will then approach the patient, confirm the initial screening for suitability and then obtain informed consent for study participation if the patient wishes to be involved in the study. Participants will be informed that their participation in the study is entirely voluntary and they are free to withdraw from the study at any time and this will have no bearing on the quality of care they receive. Patients who are unable to give informed consent due to cognitive impairment will be excluded from the trial. Patients who do not speak English will be enrolled to the trial if an interpreter is present and the patient gives informed consent through the interpreter.

Active participation in the study will be until 30 days postoperatively. At 24 h, patients will be asked to complete the QoR-15 questionnaire.

Postoperative complications will be graded using the Comprehensive Complication Index calculator (CCI^R^). This data will be acquired by using our electronic patient record system to remotely track the progress of our patients in the postoperative period. Patient progression will be monitored for the entirety of their hospital stay or for 30 days post surgery (whichever is longer).

Once the patient is discharged from hospital, there will be no further data collection. Where there is a breach in trial protocol this data will not be analysed.

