Recent best practice in anaesthesia and perioperative medicine research has been to adopt a more holistic and patient-centred approach to the evaluation of the recovery experience. The QoR-15 score is internationally recognised as a validated means of assessing patients’ quality of recovery after surgery [11]. The score assesses 5 domains of patient-reported health status: pain, physical comfort, physical independence, psychological state and emotional state to give a holistic assessment of the patient’s overall recovery experience.

Currently, opiate therapy is the primary treatment option for patients suffering acute postoperative pain after major spinal surgery. Adverse events associated with high opioid requirements postoperatively are well documented and include nausea, constipation, respiratory depression, lower respiratory tract infections and drug dependency [12]. Available evidence to date suggests the ESP block may have opioid-sparing properties [7, 9, 10], making it an attractive option in spine surgery that merits further investigation.

Additionally, the ESP block appears to be relatively simple to perform and is associated with few adverse events [13]. Alternative regional techniques such as epidural and paravertebral anaesthesia are technically more challenging to perform and are associated with significant safety risks, such as epidural haematoma or pneumothorax [14–16]. While the ESP block has been adopted enthusiastically by many anaesthesiologists, evidence showing its efficacy in improving the recovery experience and reducing morbidity for patients is lacking and therefore this clinical trial is warranted.

We hypothesise that ESP block provides superior quality of recovery and reduced morbidity compared with systemic analgesia alone. This is based on the scientific rationale that it blocks both posterior and anterior rami of the spinal nerves, thereby providing extensive block and better analgesia.

We propose a prospective, two-centre, randomised control trial of 50 patients scheduled for posterior approach thoraco-lumbar spinal surgery. The co-primary outcomes will be QoR-15 score at 24 h postoperatively and postoperative complications as measured by the Comprehensive Complication Index (CCI) score.

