#### Secondary aims

Secondary aims are to discover whether the ESP block has favourable outcomes on other metrics of patient-centred patient outcome: area under the curve (AUC) of VRS pain versus time at rest and on movement up to 24 h postoperatively, 24 h opioid consumption, time to first analgesia in recovery, length of stay (LOS) and incidence and severity of postoperative complications as measured by the Comprehensive Complication Index (CCI) score.

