### Outcome measures

Quality of recovery will be measured using the QoR-15 questionnaire. Postoperative pain will be quantified using a verbal response scale (VRS) ranging from 0 to 10, where 0 equals “no pain at all” and 10 equals “the worst pain imaginable”. Reported pain scores will then be plotted against time to give the AUC of pain versus time. Pain scores will be recorded at 6, 12 and 24 h post surgery at rest and on movement.

Postoperative complications will be graded using the Comprehensive Complication Index calculator (CCI^R^). This data will be acquired using our electronic patient record system to remotely track the progress of our patients in the postoperative period. Patient progression will be monitored for the entirety of their hospital stay or for 30 days post surgery (whichever is longer).

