This protocol will result in the attending anaesthesiologist not being blinded to the group allocation as they will be required to perform the block. This is as an unavoidable situation, as for safety reasons will we feel that the treating anaesthesiologist should be aware that their patient has received 40 ml of 0.25% levobupivacaine. However, the primary outcome is the QoR-15 score at 24 h postoperatively which will be assessed by study members blinded to the group allocation.

We have chosen to exclude patients requiring surgical intervention of five or more vertebral levels. The rational for this decision comes from cadaveric studies, which suggest the maximum spread of local anaesthetic from a single injection ESP block to be approximately 5 levels [25]. Therefore, surgical dissection beyond this point is unlikely to benefit from a single shot technique, as proposed in this trial.

Pain scores and quality of recovery will be recorded up to 24 h postoperatively. We acknowledge that for many patients having major spinal surgery their recovery will continue beyond this point. We believe that any analgesic benefit derived from a single dose of local anaesthesia is unlikely to persist beyond 24 h, and so we will not assess pain scores after this point. However, length of stay and postoperative complications will continue to be monitored after this period.

ESP blocks will be done under general anaesthesia, therefore formal dermatomal assessment of block function will not be performed. This raises the possibility that some blocks may not be fully effective. However, the practice of administering these blocks under ultrasound guidance after induction of general anaesthesia is consistent with routine clinical practice, and therefore our findings should still be applicable to widespread clinical practice.

We do not intend to assess patients’ preoperative QoR-15 in this study. Consequently, we will not have a baseline from which to compare postoperative scores and this we accept is a limitation of the study. Nonetheless, QoR-15 was designed for postoperative use, and we will apply this tool to both randomised cohorts equally. Further, the ability of QoR-15 in the immediate preoperative period to give an accurate baseline has been questioned [26].

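### The protocol gives two incompatible end points for complication data, discharge and at least 30 days, so the observation window for the Comprehensive Complication Index is not fixed

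*Protocol article*

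**What the plan says.** The protocol article describes the follow-up for complications in several places.

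- Recruitment, on participation: "Active participation in the study will be until 30 days postoperatively".
- Recruitment, and in the same terms Outcome measures, on complications: "Patient progression will be monitored for the entirety of their hospital stay or for 30 days post surgery (whichever is longer".
- Outcome measures, on the source: "This data will be acquired using our electronic patient record system to remotely track the progress of our patients in the postoperative period".
- Recruitment, in the paragraph directly after the monitoring rule: "Once the patient is discharged from hospital, there will be no further data collection".
- Discussion, after explaining why pain is not scored beyond 24 h: "However, length of stay and postoperative complications will continue to be monitored after this period". No end point is given there.

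On the standing of the outcome, Secondary aims lists "length of stay (LOS) and incidence and severity of postoperative complications as measured by the Comprehensive Complication Index (CCI) score". The Background instead states: "The co-primary outcomes will be QoR-15 score at 24 h postoperatively and postoperative complications as measured by the Comprehensive Complication Index (CCI) score".

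**The concern.** CCI accumulates: the longer a patient is observed, the more complications can be counted. A fair comparison therefore needs the same window in both arms, fixed in advance and unaffected by treatment. A rule that stops at discharge does not provide this. Discharge comes after randomisation, and the trial hopes the block will bring it forward. If it does, the ESP arm is watched for less time, and part of any CCI difference would reflect when counting stopped. Randomisation and blinded data collection do not remove that.

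There is also a practical risk. Two hospitals are taking part. Staff at one could close the record at discharge while staff at the other track it to day 30, and both could claim to be following the protocol.

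**Working it through.** The plan states no figure to reproduce. The check is a comparison of the rules, followed by an illustration of scale.

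**1. The rules side by side.** Let L be length of stay in days.

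- Discharge rule (Recruitment): window = L.
- Longer-of rule (Recruitment and Outcome measures): window = max(L, 30).
- A single fixed window, for comparison: window = 30.

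| L (assumed) | Discharge rule | Longer-of rule | Fixed window |
|---|---|---|---|
| 2 | 2 | 30 | 30 |
| 7 | 7 | 30 | 30 |
| 35 | 35 | 35 | 30 |

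The two stated rules agree only when L is 30 or more. For every earlier discharge they conflict. Take a patient discharged on day 5 and readmitted with a complication on day 12: the longer-of rule counts the event and the discharge rule does not.

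**2. Does any text reconcile them?** The discharge sentence carries no limit to patient contact or to particular outcomes, and it follows straight after the description of record-based complication tracking. The Discussion confirms follow-up beyond 24 h but gives no end. Nothing settles the conflict.

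**3. Share of a 30-day window seen under the discharge rule.** Share = L/30. The article gives no expected stay, so L = 2 to 7 days is an assumption.

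- L = 2: 2/30 = 0.067, about 7%.
- L = 7: 7/30 = 0.233, about 23%.

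These are shares of days, not of complications. If complications cluster early, the share of events captured would be larger.

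**4. Direction of a possible artefact, discharge rule only.** Assume the same true complication hazard in both arms, constant over time, with 30-day risk p. Then λ = −ln(1 − p)/30, and the risk of an event being seen by day L is 1 − exp(−λL).

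- With p = 0.20, λ = 0.2231/30 = 0.00744.
- Stay of 4 days: 1 − exp(−0.0298) = 0.029. Stay of 5 days: 1 − exp(−0.0372) = 0.037.
- Ratio, from unrounded values: 0.803.
- For p = 0.10 to 0.30, the ratio is 0.801 to 0.805 for 4 versus 5 days, and 0.717 to 0.723 for 5 versus 7 days.

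So with no true effect on complications, a difference in stay alone would give an apparent risk ratio of about 0.80 or 0.72 under these assumptions. The stays, the risks and the constant hazard are all assumed, and the result is in event risk, not CCI points. It shows direction and is not a forecast. With a fixed 30-day window the ratio is 1.

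**The case against.** The strongest reply is that the discharge sentence stands alone against the rest. Thirty-day participation is stated once and the longer-of rule twice, including in Outcome measures, where the endpoint is described. Remote tracking of the electronic record needs no patient contact and suits 30-day follow-up. The discharge sentence may have been meant only to say that contact with the patient ends. This is plausible, and it means a reader who infers that the CCI window simply is length of stay goes too far: that follows only if the discharge sentence governs. But the limit to patient contact is not written, so the conflict stands.

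The illustration is also open to challenge. Hazard after surgery need not be constant, and complications themselves prolong stay, so stay and CCI influence each other. Both points weaken the figures. Neither gives the arms a common window.

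A stronger reading is that the discharge sentence also bars the primary outcome for anyone who leaves early, since the article says "At 24 h, patients will be asked to complete the QoR-15 questionnaire". The documents do not support making this a finding. The exclusion criterion on dementia expects the questionnaire to be completed the day after surgery, Concomitant medication sends all patients to a ward with regular prescriptions, and nothing suggests discharge within 24 h of multi-level spinal surgery.

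Finally, on weight: the Abstract and Secondary aims treat CCI as secondary, and the sample size rests on QoR-15 alone. That is right, and it limits how serious the point is.

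**Conclusion.** The contradiction is real and stands in the article's own words: data collection for complications ends at discharge in one sentence and no earlier than day 30 in others. The consequence depends on which is followed. Under the discharge rule the CCI window equals length of stay, and an arm discharged earlier could show a lower CCI with no true reduction in morbidity. Under the longer-of rule everyone has at least 30 days and only stays beyond day 30 make the window vary, which is a minor matter.

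On size, an assumed stay of 2 to 7 days would leave a discharge cut-off covering about 7% to 23% of a 30-day window. The effect in CCI points cannot be derived from the documents.

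This should be fixed, but it does not threaten the primary analysis. The Background's description of CCI as co-primary makes a clear window more important. It does not change this ranking, because the sample size is built on QoR-15.

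**What to change.** Delete the discharge sentence, or limit it to direct contact with the patient. Then define CCI once, in Outcome measures, and make Recruitment agree: for every patient, all complications from surgery to day 30 inclusive, taken from the electronic patient record already being tracked, including readmissions recorded there. Following the whole hospital stay remains necessary for length of stay, but events after day 30 should not enter CCI.

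The cost is protocol wording. The data source is the one the protocol already chose, and participation is already stated as 30 days, so the fix does not depend on added telephone follow-up. The remaining weakness is that complications treated elsewhere may be missing from the record. That could affect both arms and should be stated as a limitation.

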### Randomisation and blinding

Patients will be randomised to one of the trial groups using computer-generated random number tables. Numbers ending in an even number integer will be designated to receive an ESP block; odd numbers will be allocated to the control group. The patient study number and group allocation will be typed on separate pages, folded and concealed in sequentially numbered sealed opaque envelopes. Block randomisation in groups of 6 will be applied to ensure an even number in each group as the study progresses. The groups will be named “ESP” erector spinae plane and “control”. A randomisation key will be held by an independent third party. Investigators will not have access to the randomisation key until all data is collected.

After induction of general anaesthesia, the envelope will be opened by the treating anaesthesiologist to reveal the group allocation. The investigators, patients and researchers involved in data collection will be masked to group allocation. The attending anaesthesiologist will not be blinded to the group allocation. Group allocation will be revealed immediately if deemed clinically necessary, for example, if a concern regarding local anaesthetic toxicity arises.

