### Concomitant treatment

Surgery will be performed by suitably qualified and experienced spinal surgeons. Surgical technique will vary as deemed necessary for each case. No other forms of analgesia (e.g. intrathecal opioids, epidural analgesia) will be used during the trial.

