### Study intervention

Participants randomised to the ESP group will receive an ultrasound guided bilateral ESP block post induction of general anaesthesia and prior to commencement of surgery. Blocks will be performed under full asepsis with patients in the prone position. Twenty millilitres of 0.25% levobupivacaine will be injected bilaterally at the level corresponding to the mid-point of the range of surgical dermatomes likely to be affected by the surgery. Typically, ESP will be administered at T6 level (total 40 ml). The ESP block will be performed as follows:

The approximate midpoint of the intended surgical incision will be identified first. The ultrasound transducer will then be placed approximately to 2–3 cm lateral to the midline in a longitudinal orientation to identify the hyperechoic line of the transverse process with its associated acoustic shadow. After identification of trapezius, rhomboid major and erector spinae muscle groups superficial to the transverse process, an echogenic needle will be advanced in a cranio-caudal direction. The needle tip will be advanced until it is located in the interfascial plane deep to the erector spinae muscle group and superficial to the transverse process. Once in position, 20 ml 0.25% levobupivicaine will be injected under ultrasound guidance. Correct needle tip position will be confirmed by the presence of linear spread between the transverse process and the erector spinae muscle group. The same process will then be repeated on the opposite side at the same vertebral level. Because patients will be under general anaesthesia during the block performance, no formal dermatomal sensory testing of block efficacy will be performed. Surgery will commence once the block is completed. There will be no further intervention to the routine conduct of surgery and anaesthesia after this point. Blocks will be performed by anaesthesiologists with subspeciality training in regional anaesthesia. To improve adherence to the intervention protocol, anaesthesiologists will be asked to document the block performance in the anaesthesiology patient record. Although the ESP has been established as a safe means of providing analgesia in spine surgery, we will make all our data available to local data monitoring committee.

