### Statistical considerations

Data will be inspected and tested for distribution according to the Kolmogorov-Smirnov test. Normally distributed data will be compared between study arms using the unpaired *t* test, whereas non-normally distributed data will be compared using the Mann-Whitney *U* test. All data will be summarised as mean + SD or median (25–75% range) as appropriate.

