### Sample size and justification

The primary outcome of this study will be the QoR-15 score at 24 h postoperatively. The established minimum clinically important difference in QoR-15 is 8.0 and the mean SD of QoR-15 scores after major spinal surgery is in the order of 14 [range of QoR score is 1–150]. Therefore, assuming type I error = 0.05 and type II error = 0.2 (80% power to detect this difference), then *n* = 25 patients will be required in each group. To accommodate for participants who may withdraw from the study, we will aim to recruit *n* = 26 patients to each study arm.

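### The only stated analysis-set rule discards data after any protocol breach, so the randomised comparison is open to selection bias of unknown direction and size

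*Protocol article*

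**What the plan says.** The rule stands at the end of the Recruitment section of the protocol article: "Where there is a breach in trial protocol this data will not be analysed". Breach is not defined there, and the sentence separates neither breaches before allocation from those after it nor minor from major ones.

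Other sections that bear on it:

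- **Randomisation and blinding** fixes when the arm becomes known: "After induction of general anaesthesia, the envelope will be opened by the treating anaesthesiologist to reveal the group allocation". It adds: "The attending anaesthesiologist will not be blinded to the group allocation".
- **Study intervention** describes the block, which only the ESP arm should receive, and how its delivery is recorded: "To improve adherence to the intervention protocol, anaesthesiologists will be asked to document the block performance in the anaesthesiology patient record".
- **Concomitant treatment** sets a restriction for both arms: "No other forms of analgesia (e.g. intrathecal opioids, epidural analgesia) will be used during the trial". Concomitant medication also rules out remifentanil and ketamine.
- **Statistical considerations** names the tests ("Normally distributed data will be compared between study arms using the unpaired" *t* test, otherwise Mann-Whitney) but not the patients to whom they apply.
- **Sample size and justification** plans 25 per group and recruits 26, the extra patient being for withdrawals.
- **Exclusion criteria** lists postoperative ICU admission for continued ventilation, without saying whether this means planned or unplanned admission.

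**The concern.** Randomisation makes the arms comparable at the moment of allocation. That holds in the analysis only if patients are kept or dropped for reasons unrelated to what happens afterwards. A rule that removes data because of a breach selects on events after allocation, and here those events need not be balanced:

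- A block omitted, abandoned or given off-specification can occur only in the ESP arm. A block given in error can occur only in the control arm.
- Prohibited analgesia can occur in either arm and is plausibly more likely when pain is worse, which ties it to QoR-15, pain scores and opioid use.
- The clinician who directs intraoperative care knows the arm.

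Masked outcome assessors do not solve this. Even if the person who classified breaches were masked, the breaches themselves depend on the arm and on the patient's course.

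At stake is the primary comparison. It would estimate an effect in patients whose care went to plan, who are not necessarily alike in the two arms. The Discussion argues that the findings should apply to routine practice even though some blocks may not work fully. An analysis as randomised serves that aim, and the breach rule works against it.

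**Working it through.** **1. Order of events.** Consent, induction, envelope opened, block (ESP arm), surgery, PACU and ward analgesia, QoR-15 at 24 h. Every breach listed above falls after the envelope is opened.

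**2. The plan's own figures.** No breach rate or expected number of exclusions is stated. The recruitment margin is 26 − 25 = 1 per arm, or 1/26 = 3.8%, and is assigned to withdrawals. The stated 25 per group does not reproduce as a two-group comparison:

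- Two-sample: 2 × (14 × (1.960 + 0.842)/8)² ≈ 48.1, so 49 per group.
- Without the factor 2: (14 × (1.960 + 0.842)/8)² = 24.04, so 25.

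That is a separate point. It matters here only because it sets the baseline for the power figures in step 5.

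**3. Shift in an arm mean.** Suppose k of n patients in an arm are dropped and their mean is D points below that of the retained patients. The full-arm mean is then the retained mean minus (k/n) × D, so dropping them raises the arm mean by (k/n) × D.

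Inputs: n = 25, SD = 14 and the 8-point important difference come from Sample size and justification ("The established minimum clinically important difference in QoR-15 is 8.0"). **k and D are assumptions.**

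| Dropped, one arm only | D (points) | Shift in that arm's mean |
|---|---|---|
| 1 of 25 | 7 (0.5 SD) | 1/25 × 7 = 0.28 |
| 3 of 25 | 14 (1 SD) | 3/25 × 14 = 1.68 |
| 5 of 25 | 28 (2 SD) | 5/25 × 28 = 5.6 |

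The middle row is 1.68/8 = 21% of the important difference. With 26 per arm it is 3/26 × 14 = 1.62. The last row is extreme: a fifth of one arm dropped, 2 SD worse, and none dropped from the other.

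**4. Direction.** The sign depends on which arm loses patients. In the middle row, losses from ESP move the difference 1.68 points towards ESP, losses from control move it 1.68 points away, and equal losses of equal prognosis in both arms cancel. D could also be negative if patients with a breach fare better than the rest. The documents do not settle which case applies.

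**5. Power.** Two-sided *t* test, difference 8, SD 14, noncentrality 8/(14 × √(2/n)):

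- n = 25: noncentrality 2.02, power 50.8%.
- n = 22 (three lost per arm): noncentrality 1.90, power 45.7%.

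The loss due to exclusions is about 5 percentage points. The low starting value belongs to the sample-size point.

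**The case against.** The best defence is that the sentence is brief, sits under Recruitment after a remark on data collection ending at discharge, and leaves breach undefined. The phrase could mean only the affected data items, and an analysis plan that is not shown could define breaches narrowly. The first part is possible, but the plain wording still withholds data from analysis because of a breach. On the second, the article does not leave the analysis set open. It states a rule, and an analysis plan that analysed patients as randomised would contradict it.

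Four stronger readings are tempting, and the documents do not support them:

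- *The rule favours ESP.* A reader might infer this from ESP-arm blocks that go wrong. If the block works, however, prohibited analgesia would be used mainly in controls with more pain, and dropping them raises the control mean. The mechanisms oppose each other.
- *Ineffective blocks would be dropped.* Study intervention says that block efficacy will not be formally tested, and the Discussion accepts that some blocks may not be fully effective. An ineffective block is neither detected nor called a breach. Likewise, as-required oxycodone is within protocol, so heavier use of it is not a breach.
- *ICU ventilation is an established post-randomisation exclusion.* The item is worded as a postoperative event, but it stands among features known or planned before surgery and may mean planned ventilation. No section says that a randomised patient with unplanned ICU ventilation leaves the analysis or follow-up. It is an ambiguity.
- *A shift in CCI can be quantified.* Dividing an assumed score for one dropped patient by the arm size would treat every retained patient as scoring 0. The article gives no CCI distribution, so no figure is offered.

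**Conclusion.** The point stands for the breach rule. It is explicit and unlimited, it is the only statement on who is analysed, and it acts on events after allocation. Followed as written, it makes the primary analysis per-protocol, with selection bias of unknown direction and size.

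The 1.7-point figure is an illustration. It assumes three exclusions in one arm only, with scores 14 points below the rest, and neither assumption comes from the documents. The range of 0.28 to 5.6 points shows how strongly the result depends on them. It is certain, however, that one withdrawal per arm exhausts the recruitment margin, so any exclusion for breach beyond that takes the arm below its planned size.

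The ICU criterion needs clarification and is not a demonstrated error. Because the remedy is wording and the rule governs the primary comparison, it should be settled before the data are analysed.

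**What to change.** Replace the breach sentence with: *all randomised patients are analysed in the group to which they were allocated, whatever breaches occur; breaches are reported by arm, and an analysis excluding them is a per-protocol sensitivity analysis.*

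State that the ICU ventilation criterion applies only to what is known before randomisation. State also that randomised patients with unplanned ICU ventilation stay in follow-up and in the CCI and length-of-stay analyses, with missing QoR-15 reported by arm.

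The cost is a change of wording in the protocol, carried into the analysis plan. No extra patients or measurements are needed. The downside is that the estimate may be slightly diluted by non-adherence, which the sensitivity analysis would help to show.
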